### 13.3 Adverse Event follow-up procedures

Adverse Events will be followed up throughout the course of the clinical trial.

### 13.4 Potential Risks and Potential Adverse Events

As proposed treatment is in line with normal procedures in elective pancreatic surgery no additional risk is considered to arise from the present study.

According to the SmPCs for Tetraspan (10% and 6%) and for Sterofundin ISO the following adverse drug reactions are described:

**Tetraspan:** The most common side effects observed are directly related to the therapeutic effect of starch solutions and the doses given, i.e. dilution of the blood as a result of the filling of the intravascular space without administering blood components at the same time. Coagulation factor dilution can also occur.

**Sterofundin ISO:** Overdose or too fast administration may lead to water and electrolyte (including acetate, malate) overload with respective signs and symptoms as described in SmPC section overdose.

#### Blood and lymphatic system disorders

**Tetraspan:** Very common: Decreased haematocrit and reduced concentration of plasma proteins due to dilution. Common (depending on the administered dose): Relatively large doses of hydroxyethyl starch result in dilution of coagulation factors and can therefore affect blood coagulation. Bleeding time and aPTT can be prolonged and the level of FVIII/vWF complex can be reduced after administration of large doses.

#### Immune system disorders

**Tetraspan:** Rare: Anaphylactoid reactions of varying degrees. Hypersensitivity reactions which occur very rarely are not dose-dependent.

**Sterofundin ISO:** Occasionally: Hypersensitivity reactions characterized by urticaria have been occasionally described after the intravenous administration of magnesium salts.

### Gastrointestinal disorders

Sterofundin ISO: Rare: Although oral magnesium salts stimulate peristalsis, paralytic ileus has been rarely reported after intravenous infusion of magnesium sulphate.

### General disorders and administration site conditions

Tetraspan: Uncommon: Repeated infusions of HES for several days, particularly when high cumulative doses are reached, generally result in itching which responds poorly to any therapy. This itching can occur several weeks after the end of the starch infusions and can persist for months. The probability of this undesirable effect has not been sufficiently studied with Tetraspan 10% and Tetraspan 6%

Sterofundin ISO: Adverse reactions may be associated to the technique of administration including febrile response, infection at the site of injection, local pain or reaction, vein irritation, venous thrombosis or phlebitis extending from the site of injection and extravasation.

### Laboratory investigations

Tetraspan: Very common: Infusion of hydroxyethyl starch results in increased serum alpha-amylase levels. This effect is a result of the formation of an amylase complex of hydroxyethyl starch with delayed renal and extrarenal elimination. This should not be misinterpreted as evidence of a pancreatic disorder.

## **13.5 Pregnancies**

If a female patient gets pregnant while participating in the present study this event has to be recorded and reported using the Serious Adverse Event Reporting Form (template see annex 8). If possible outcome of birth should be recorded.

## **14 VISIT SCHEDULE**

### **14.1 Procedures at Each Visit**

**day -1** (range -5)/ pre-operatively:

- Verification of inclusion and exclusion criteria\*, including informed consent
- History, demographics, body weight
- Randomization
- HRQoL (EQ-5D questionnaire)
- Pre-operative medication / therapy as medically indicated and standardized (including pre-operative fasting time, type of bowel preparation)
  - Pre-op transfusion will be administered according to standard procedure (hct. between 25 and 30%)

\* blood samples for laboratory evaluation of haematocrit, renal function/serum creatinine, hepatic function/Quick value, Child-Pugh, electrolyte status/ Na, K, Ca

\* urine sample in women: for pregnancy testing

**day 0**/ prior anaesthesia:

- Start basal infusion of crystalloid fluid replacement: 4 ml/kg/h
- Insert thoracic epidural catheter
- Induction anaesthesia
- Adverse events

**day 0/** after induction of anaesthesia/prior surgery :

- Set arterial line and central venous catheter
- After set of urethral catheter measurement of intraabdominal pressure
- Final positioning of patient in operating theatre
- Placement of oesophageal probe, calibration of PiCCO
- Baseline recording of haemodynamics (SAP, DAP, MAP, HR, CVP; oesophageal Doppler and PiCCO: CI, SV, SVR; PiCCO: ITBVI, EVLWI)
- Body temperature
- Blood sampling and urine sample for laboratory evaluation\*
- Concomitant medication and therapy (including concomitant medication prior induction of anaesthesia; including blood products acc. to trigger)  
Note: Loading dose of epidural analgesia will be applied at the end of surgery after all intraoperative study related measurements have been finalized
- Adverse events

## Baseline laboratory

- arterial blood gas analysis (pCO2, pO2, HCO3, SaO2) including acid base status (pH, BE, lactate, bicarbonate) and electrolytes (Na, K, Ca, Cl). Blood sampling for BGA should be performed as close as possible to the time, at which the corresponding hemodynamic measurement is done.
- renal function parameters (*urine*: creatinine,  $\alpha$ 1-MG,  $\beta$ -NAG; *serum*: creatinine, BUN, HbA1c)
- haemostasis and coagulation parameter (PT, aPTT, Fibrinogen, vWF-Ag, vWF-RiCo, F VIII:c; CT, CFT, MCF using ExTEM und FibTEM)
- Inflammamatory parameters (IL6 (facultative), IL 10 (facultative), PCT, CRP, white blood cell count (WBC))
- cardiac function parameters (Troponin or high-sensitivity Troponin, NT-Pro-BNP)

**day 0/** after baseline recordings:

- First bolus (250 mLs/5 min) of Investigational Products
- Start of volume replacement algorithm according to oesophageal Doppler measurements
- Thereafter: start of surgery/skin incision
- Adverse events and adverse reactions

**day 0/** during surgery (after start of skin incision):

- Haemodynamics
  - every 15 min within dosing algorithm cycle when there is no volume optimisation, or 15 minutes after stroke volume optimisation: SAP, DAP, MAP, HR, CVP; PiCCO and oesophageal Doppler: CI, SV, SVR
  - every 60 min after start of surgery: ITBVI, EVLWI (PiCCO)
- Infusion of the Investigational Products according to algorithm
- Hourly blood sampling for intraoperative laboratory evaluation\*
- Diuresis/urinary output (cumulative every 60 min)
- Concomitant medication and therapy (including inotropic drugs, sodium bicarbonate, infusion of blood products (RBC, FFP, platelets) according to the triggers
- Adverse events and adverse reactions

\*laboratory measurements in blood/serum samples:

- 1 hour after start of surgery: haemostasis/ coagulation (ROTEM only), arterial blood gas analysis (pCO2, pO2, HCO3, SaO2) including acid base status (pH, BE, lactate, bicarbonate) and electrolytes (Na, K, Ca, Cl)
- at 2 hours after start of surgery and then every 60 min intraoperatively: arterial blood gas analysis (pCO2, pO2, HCO3, SaO2) including acid base status (pH, BE, lactate, bicarbonate) and electrolytes (Na, K, Ca, Cl)
- blood sampling for BGA should be performed as close as possible to the time, at which the corresponding hemodynamic measurement is done. i.e. ITBVI and EVLWI.

**day 0/** at the end of surgery:

- Haemodynamics (SAP, DAP, MAP, HR, CVP; PiCCO and oesophageal Doppler: CI, SV, SVR; PiCCO: ITBVI, EVLWI)
- intraabdominal pressure (still in operating theatre directly before extubation)
- Concomitant medication and therapy, blood products
- Blood sampling for laboratory evaluation\*
- Investigational Products
- Diuresis/urinary output
- Adverse events and adverse reactions
- Loading dose of epidural analgesia will be applied at the end of surgery after all intraoperative study related measurements have been finalized

## \* laboratory measurements in blood/serum sample:

- arterial blood gas analysis/acid base status/electrolytes. Blood sampling for BGA should be performed as close as possible to the time, at which the corresponding hemodynamic measurement is done.
- haemostasis/coagulation parameters (PT, aPTT, Fibrinogen, FVIII:c, vWF-Ag, vWF-RiCo; CT, CFT, MCF using ExTEM und FibTEM)
- cardiac function (Troponin or high-sensitivity Troponin, NT-Pro-BNP)
- inflammatory reaction parameters (facultative: IL-6, IL-10)

**day 0/** intensive care unit (ICU) –

- Aldrete Score (*on admission*)
- Haemodynamics (SAP, DAP, MAP, HR, CVP (on admission and 6hourly); PiCCO: CI, SV, SVR, ITBVI, EVLWI) (on admission and after 6 hours)
- blood gas analysis (arterial or venous blood sample) including acid base status and electrolytes: (on admission, 6 hours after admission). Blood sampling for BGA should be performed as close as possible to the time, at which the corresponding hemodynamic measurement is done.
- abdominal pressure (*6 hours after admission*)
- Ventilatory support as requested to maintain normocapnia and oxygen saturation (PCV, CPAP)
- Concomitant medication, infusion therapy (separate for colloids (i. e. gelatine) crystalloids, blood products)
- Diuresis (sampling period until next morning about 6 o'clock)
- Adverse events and adverse reactions

- check of discharge criteria

**day +1** (1st post-operative day)/ On ICU: Postoperative care will follow a standardised regimen.

- Haemodynamics (SAP, DAP, MAP, HR, CVP(every 6 hours)); PiCCO: CI, SV, SVR, ITBVI, EVLWI (every 12 hours/ in the morning and in the evening)
- abdominal pressure (in the morning)
- Ventilatory support (PCV, CPAP) as requested to maintain normocapnia and oxygen saturation
- Blood sampling for laboratory evaluation\*, urine sample for laboratory evaluation\*\*
- Aldrete Score (in the morning)
- SIRS-criteria
- Nursing Delirium Screening Scale (NuDesc) (three times daily)
- Injury scores (APACHE II, SAPS II, SOFA)
- Assessment of “fit for discharge” criteria (once on ICU - preferably in the morning)
- Concomitant medication including parenteral nutrition, infusion therapy (separate for colloids i. e. gelatine and crystalloid, blood products)
- Diuresis (Sampling period is from morning until next morning about 6 o'clock)
- PONV
- body weight (if possible)
- Gastrointestinal parameters (bowel movement on auscultation, time to full oral nutrition, time to first defaecation, time to first flatus)
- Adverse events and adverse reactions
- Check of discharge criteria

\* laboratory measurements in blood/serum samples 1st post-operative day:

- in the morning sample: Troponin or high-sensitivity Troponin, NT-Pro-BNP, IL6 (facultative), IL10 (facultative), PCT, CRP, WBC, creatinine, BUN, PT, aPTT, vWF-Ag, vWF-CoRi, ROTEM
- every 6 hours: blood gas analysis/acid base status/electrolytes (arterial or venous blood sample). Blood sampling for BGA should be performed as close as possible to the time, at which the corresponding hemodynamic measurement is done.
- additional for injury scores: bilirubin, thrombocytes, haematocrit

\*\*\*laboratory measurements in urine sample: creatinine,  $\alpha$ 1-MG,  $\beta$ -NAG

**day +2 – +n**, until fulfillment of “fit for discharge”-criteria (Marshall, Chung 1997, 1999) however not longer than day +5 (including day +5) (*blood sampling also on postoperative day +3 and +7*)

- Haemodynamics (SAP, DAP, MAP, HR, CVP(every 6 hours); PiCCO: CI, SV, SVR; ITBVI, EVLWI (every 12 hours))
- Ventilatory support (PCV, CPAP) as requested to maintain normocapnia and oxygen saturation
- Blood sampling/urine sampling for laboratory evaluation (daily)\*
- SIRS-criteria
- NuDesc (3x daily)
- Injury scores (APACHE II, SAPS II, SOFA) (once daily)

- Concomitant medication, infusion therapy (separate for colloid (gelatine) and crystalloid, blood products)
- Diuresis (sampling period from morning until next morning about 6 o'clock)
- PONV
- Surgical complications (e.g. anastomotic insufficiency, intestinal leakage, wound healing)
- Gastrointestinal parameters (bowel movement on auscultation, start of enteral nutrition, time to first defaecation)
- Mobilisation
- "Fit for discharge"-criteria (Marshall, Chung, 1997, 1999) (once on ICU-preferably in the morning)
- Aldrete Score (assessment at time when discharge from ICU)
- Adverse events and adverse reactions
- check of discharge criteria

\*laboratory measurements on ICU

- once daily on ICU (maximally until day 5 (including day 5): renal function parameters (blood/serum: creatinine, BUN; urine: creatinine,  $\alpha$ 1-MG,  $\beta$ -NAG), WBC
- additional for injury scores: arterial pH, haematocrit, Sodium, Potassium, HCO3, bilirubin, platelets
- postoperative days 3 and 7: creatinine in serum

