
\* if not otherwise mentioned measurements of secondary variables on ICU will be performed until fit-for-discharge from ICU criteria are fulfilled or until postoperative day 5 (including), whatever occurs first.

Efficacy:

- Haemodynamics
  - SAP, DAP, MAP, HR, CVP, CI, SV, SVR
  - cumulative dose of norepinephrine (mcg/h)
  - intrathoracic blood volume index (ITBVI) and extravascular lung water index (EVLWI), (PICCO)
- Time on ventilator (*measured from intubation in hours; the need of reintubation will be documented*)
- Requirements of postoperative ventilatory support (PCV, CPAP)
- Nursing Delirium Screening scale (NuDesc) – *measurement three times daily on ICU\**
- gastrointestinal parameters - (*measurement daily from post-op day +1 until fulfilment or until end of study, whatever occurs first*)
  - time until bowel movements (on auscultation)
  - time until full oral nutrition
  - time to first flatus
  - time to first defecation
  - intraabdominal pressure *measured baseline (after induction of anaesthesia), at the end of surgery (still in operating theatre before extubation), 6 hours after surgery, 1st post-operative day in the morning*
- SOFA, SAPS II, APACHE II Scores – *surveyed once daily on ICU\**
- length of stay in ICU/IMCU (fulfillment of ICU/IMCU release criteria according to the Aldrete Score, Aldrete 1995) *surveyed on admission to ICU, 1st postoperative day in the morning, at time of discharge from ICU*
- time until criteria for “fit for discharge from hospital” are fulfilled (hospitalization release criteria according to Marshall et al., 1999, Marshall and Chung, 1997) *surveyed once daily on ICU respectively surgical ward (if fit-for-discharge criteria are not fulfilled within the 5th postoperative day it will be controlled until fulfillment or until end of study, whatever occurs first)*
- Complication rate - surgical complications such as re-do surgery (e. g. anastomotic insufficiency or bowel leakage), disturbed wound-healing or medical complications which delay time to fully oral nutrition – *documentation at the study end*
- combined outcome parameter of prolonged length of stay (based on mean length of stay according to the German Diagnosis Related Group System D-DRG) or death (determination will be when DRG-data are available, i. e. after study end)
- Health Related Quality of Life (HRQoL) according to the EQ-5D questionnaire – *measurement baseline and 3 months after surgery*

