|  | 
(facultative), IL10 (facultative), PCT, CRP, WBC, creatinine, BUN, PT, aPTT, vWF-Ag, vWF-CoRi, ROTEM, platelet count
 
 
o every 6 hours: blood gas analysis/acid base status/electrolytes. Blood sampling for BGA should be performed as close as possible to the time, at which the corresponding hemodynamic (SAP, DAP, MAP, HR and CVP) measurements are done.
 
 
**laboratory measurements in urine sample: <math>\alpha</math>1-MG, creatinine, <math>\beta</math>-NAG
 
day +2 – day +n, until fulfillment of “fit for discharge”-criteria (Marshall and Chung 1997, 1999) however not longer than until day +5 (including day +5) (blood sampling also on (postoperative) day +3 and +7)
 
 
▪ Haemodynamics (SAP, DAP, MAP, HR, CVP(every 6 hours); PiCCO: CI, SV, SVR; ITBVI, EVLWI (every 12 hours))
 
▪ Ventilatory support (PCV, CPAP) as requested to maintain normocapnia and oxygen saturation
 
▪ Blood sampling/urine sampling for laboratory evaluation (daily)*
 
▪ SIRS-criteria
 
▪ NuDesc (3x daily)
 
▪ Severity of injury scores (APACHE II, SAPS II, SOFA) (once daily)
 
▪ Assessment of “fit for discharge” criteria (once on ICU-preferably in the morning)
 
▪ Concomitant medication, infusion therapy (separate for colloid (gelatine) and crystalloid, blood products)
 
▪ Diuresis (sampling period from morning until next morning about 6 o'clock)
 
▪ PONV
 
▪ Surgical complications (anastomotic insufficiency, intestinal leakage, wound healing)
 
▪ Gastrointestinal parameters (bowel movement on auscultation, start of enteral nutrition, time to first defaecation)
 
▪ Mobilisation
 
▪ “Fit for discharge”-criteria (Marshall and Chung, 1997, 1999) : fit for discharge criteria will be controlled until fulfilled or until study end, whatever occurs first
 
▪ Aldrete Score (assessment at time when discharge from ICU)
 
▪ Adverse events and adverse reactions (continuously until postoperative day 5, serious adverse events that are not yet resolved on POD 5 will be followed up until study end)
 
 
*laboratory measurements on ICU, respectively on (postoperative) days +3 and +7
 
 
o once daily on ICU (max. for 5 days): renal function parameters (blood: creatinine, BUN), platelet count, WBC, blood gas analysis (pH, HCO3, sodium, potassium, Hct) for scores; urine:
 
 |

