### Other

Aldrete Score (refer to in Marshall et al. 1999, appendix 8): on admission to ICU and once daily on ICU.

Length of stay in ICU/IMCU (fulfillment of discharge criteria) – assessment will be done once daily (evening) on ICU. If fit-for discharge criteria are not yet fulfilled at POD 5 it will be continued to check until fulfillment or until study end, whatever occurs first.

Morbidity and complication rate: surgical complications such as re-do surgery (e. g. anastomotic insufficiency or bowel leakage), disturbed wound-healing or medical complications which delay time to fully oral nutrition will be assessed and documented at study end

Combined outcome parameter of prolonged length of stay (based on mean length of stay according to the German Diagnosis Related Group System D-DRG) or death.

Health Related Quality of Life (HRQoL) before and 3 months after surgery (EQ-5D, the EuroQol Group, <http://www.euroqol.org>)

**NOTE:** measurements on ICU (if not otherwise mentioned) will be performed until “fit for discharge criteria are fulfilled or until day +5 (incl. day +5) whatever occurs first.

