20= serum creatinine

**\*Time n usually (if not otherwise mentioned) is defined as time when patient ready for discharge (exception of nutrition control) maximally until postoperative day 5 (including POD 5)**

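### The protocol contradicts itself on how long bowel recovery is recorded after day +1, and its day +2 to +n lists omit first flatus

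*Protocol*

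**What the plan says.** Under secondary efficacy variables, the synopsis lists four gastrointestinal parameters (bowel movements on auscultation, full oral nutrition, first flatus, first defaecation) and gives them a window of their own: "measurement daily from post-op day +1 until fulfilment or until end of study, whatever occurs first". Section 15.1 sets the end of study at POD 15 or hospital discharge, whichever comes first.

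The visit schedules differ. For day +1, section 14.1 lists "Gastrointestinal parameters (bowel movement on auscultation, time to full oral nutrition, time to first defaecation, time to first flatus". From day +2 the parameters sit in a block that ends once the fit-for-discharge criteria are met, "however not longer than day +5 (including day +5", and the list becomes "Gastrointestinal parameters (bowel movement on auscultation, start of enteral nutrition, time to first defaecation". First flatus has gone, and the start of enteral nutrition stands where full oral nutrition stood. The synopsis's own visit schedule has the same shortened list and the same limit, "however not longer than until day +5 (including day +5".

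Two general rules sit beside these. The NOTE in section 12.3 continues ICU measurements until "fit for discharge criteria are fulfilled or until day +5 (incl. day +5) whatever occurs first". The footnote to the 14.2 overview says that time n "is defined as time when patient ready for discharge (exception of nutrition control) maximally until postoperative day 5". Both begin with a proviso that they hold unless something else is stated.

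First flatus remains a variable in section 12.3 and a CRF item in section 12.5. The gastrointestinal row of the 14.2 overview is ticked both for day +1 and for day +2 to +n.

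**The concern.** Site staff usually work from the visit schedule. One that follows the day +2 to +n block would stop looking for a first defaecation when the patient is fit for discharge, or on day +5, and would find no prompt for flatus after day +1. Follow-up would then depend on recovery, the process these variables measure: fast recoverers are watched for the shortest time, and events after day +5 go unseen.

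This affects the analysis. Section 16.1 foresees nonparametric tests for secondary variables, and section 16.5 says missing values will not be imputed. If a patient without the event at the stop counts as missing, the remaining times describe a selected subset. These are also the secondary measures closest to the second primary endpoint, time to full oral diet, which they would naturally be read alongside. With three centres (section 8), different sites could apply different windows.

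**Working it through.** The protocol states no figure on this point, so the check is mainly a comparison of places.

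| Place | Window after day +1 | First flatus after day +1 |
|---|---|---|
| Synopsis, secondary efficacy variables | to fulfilment or end of study | yes |
| Synopsis, visit schedule, day +2 to +n | to fit for discharge, day +5 at most | absent |
| Section 12.3, variable list | none given | yes |
| Section 12.3, NOTE | same day +5 stop, as a default | not addressed |
| Section 12.5, source documents | none given | CRF item |
| Section 14.1, day +2 to +n | to fit for discharge, day +5 at most | absent |
| Section 14.2, table and footnote | same day +5 stop, as a default; nutrition control excepted | whole row ticked, flatus not excluded |

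**Do the defaults settle it?** Partly. The NOTE and the footnote give way to anything stated elsewhere, and the synopsis variable list does state a longer window. The day +2 to +n block has no such proviso. Its heading excepts only blood sampling on days +3 and +7. In the synopsis copy, two other items carry their own longer follow-up (fit-for-discharge checks, and unresolved serious adverse events), but the gastrointestinal line carries none. The conflict therefore remains, and it also lies within the synopsis.

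**Difference in recording days.** The variable list allows up to 15 days, fewer if the patient leaves hospital or has the event sooner. The block allows at most 5, and only days +1 and +2 for a patient fit for discharge on day +2. Read literally, its list leaves flatus with day +1 alone.

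**Share of event times affected.** This needs a distribution that the documents do not give. As an assumption only, take lognormal event times with median m days and log-SD s. The share with the event after day 5 is 1 − Φ(ln(5/m)/s). For m = 4 and s = 0.3, ln(5/4) = 0.223; 0.223/0.3 = 0.744; 1 − Φ(0.744) = 23%.

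| Assumed median (days) | After day 5, s = 0.3 | After day 5, s = 0.5 |
|---|---|---|
| 2 | 0% | 3% |
| 3 | 4% | 15% |
| 4 | 23% | 33% |
| 5 | 50% | 50% |
| 6 | 73% | 64% |

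With 15 in place of 5, and no discharge before then, the share is at most about 3% in every row. If flatus were asked on day +1 only, the share with a later first flatus, 1 − Φ(ln(1/m)/s), would be 50% at m = 1 and about 92% or more at m = 2 to 4. The results range from negligible to a majority, so they do not establish a size.

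**The case against.** The best defence is that the synopsis variable list gives a specific rule for these parameters, and that the NOTE in 12.3 and the 14.2 footnote are defaults that yield to it. That stands for those two places: a reader might infer that the footnote spares nutrition control alone, but its opening proviso also spares anything specified elsewhere. The defence does not reach the day +2 to +n block, which sets its limit without that proviso.

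Several stronger readings are tempting and are not supported:

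- That the synopsis is right and the body wrong. The synopsis contains both versions.
- That flatus would certainly be asked once only. Sections 12.3 and 12.5 and the ticked row in 14.2 keep it alive; only the bracketed lists in the two visit schedules omit it. A site could still record it.
- That event times are lost for many patients. No event-time data are given, and a patient without the event at the stop is in principle right-censored at a known time.
- That starting enteral nutrition is an irrelevant item. Absence of enteral nutrition is part of the definition of the second primary endpoint, so there is a reason to ask about it.

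It is also fair to say that the effect is limited. Section 16.2 makes tests of secondary variables exploratory. Full oral diet is followed separately up to day +15 (sections 11 and 14.1).

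**Conclusion.** The contradiction is real. The protocol gives two recording windows for bowel movements and first defaecation, and its day +2 to +n lists leave out first flatus, which it defines as a variable. Sites following the visit block could stop early, at a time that depends on recovery, and not ask about flatus after day +1.

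The size cannot be determined: it depends on which wording sites follow and on event-time distributions that the documents do not contain. The percentages above illustrate sensitivity to the assumed median and are not estimates for this trial. No confirmatory conclusion is touched. The point is an internal inconsistency in exploratory secondary data, worth correcting because event times not recorded on the ward may not be recoverable later.

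**What to change.** Adopt the window already stated in the synopsis variable list and align the other places with it:

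1. In the day +2 to +n blocks of the synopsis and section 14.1, in the 12.3 NOTE and in the 14.2 footnote, exempt bowel movements, first flatus and first defaecation from the fit-for-discharge/day +5 stop, as is done for nutrition control. Record each daily from day +1 until it occurs or the study ends.
2. Restore first flatus to the day +2 to +n lists in the synopsis and section 14.1.
3. Analyse a patient without the event at hospital discharge or POD 15 as censored at that time, not as missing. The SAP is not at hand and may already say this; if so, only the schedule wording needs changing.

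The cost is small. A daily nutrition check already runs on the ward to day +15 at most. It stops when full oral diet is reached, so the extra data entry falls on patients who eat before these events occur. The change does not remove truncation at hospital discharge, so patients who leave early are still observed for less time.
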